### Study design and overview

Study participation will last 6 weeks and include 3 virtual visits (10–40 minutes each; baseline, quit date, and end of the study) and 5 daily EMAs for 42 days. After the baseline visit, participants will complete daily EMAs for 2 weeks in the pre-quit period and for 4 weeks in the post-quit period (see Fig 1). Participants will be required to complete EMAs 30 minutes after their preset waking time (morning diary), 3 random times (random sampling) during each day and one hour before bedtime (evening diary), to assess any smoking-related triggers and behaviors and smoking events and to complete biochemical verification of smoking status via iCO Breathlyzer in the evening [40] Participants can also initiate prompts when they smoke. In addition, participants will wear an ActiWatch (Motion Watch 8; CamNTech, Ltd) [41] during the 6-week study period (See Measures section for details). Participants will complete a follow-up assessment 4 weeks after their end of study to assess relevant variables including smoking status.

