### Procedure

Participants will be provided an Actiwatch, and an iCO Breathalyzer. Participants who do not have a smartphone that meets the minimum criteria to support the Insight^TM^ app [44] will also be provided a phone. Participants will be instructed regarding using the Insight^TM^ smartphone application, Actiwatch, Breathalyzer, and EMA procedures. Participants will complete questionnaires at the baseline visit, including the pre-treatment assessment of sleep, other tobacco use, past/current medical history, provide a CO breath sample to verify smoking status, and measure of neck circumference.

Participants will use the Insight^TM^ app [44] to record subjective sleep and wake times and will wear an Actiwatch to obtain objective sleep data continuously for the entire 6-week study period. At the end of the study, participants will return the Actiwatch and study phone (if they did not use their own smartphone) via mail or curbside drop-off. All participants will download the Insight^TM^ mHealth application [44], which includes a “Call Staff” function/button that automatically calls study staff (e.g., if the participant has problems completing EMAs). The Insight^TM^ app [44] also includes a “Payment” button which, when pressed, indicates the number of EMAs that have been prompted and completed and the current level of compensation based upon the up-to-the-moment percentage of EMAs completed. All participants will wear Actiwatch, complete 3 virtual visits, and complete 5 daily EMAs (i.e., 3 random,1 morning and 1 evening diaries; see Measures section for details). Participants will receive $15 for completing each visit ($45 in total) and will be compensated based upon the percentage of Daily and Random EMAs completed (i.e., $70 for completing 50%−74% of prompted EMAs, $90 for completing 75%−89% of prompted EMAs, and $120 for completing 90% or more prompted EMAs). An additional $50 payment will be awarded to participants for wearing the Actiwatch at least 90% of the time. This payment will be provided after participants return the Actiwatch. There will be additional $10 payment for those who complete the one-month follow-up survey. The use of personal vs. study-provided phones will be examined as a covariate in all analyses. Data collection is expected to be completed by August 2028.

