### Analytic approach

Descriptive statistics will summarize the distributions of outcomes and demographic characteristics. We will also explore any differences in outcomes by demographic characteristics (e.g., sex, race). If more than 10% of the outcomes are missing, methods for missing data will be considered. To identify bidirectional and temporal associations of daily abstinence and sleep dysregulation via EMA and wrist worn sensors during the first four weeks of a smoking cessation attempt (N = 80), cross-lagged models (see Fig 2) will be tested to examine 1 simultaneously) the association of sleep dysregulation with subsequent changes in daily abstinence, and 2) the association of daily abstinence with subsequent changes sleep dysregulation using Actiwatch. We will use multilevel models with lagged effects in SAS 9.4 software (SAS Institute, Cary, North Carolina) to test the temporal associations between daily sleep dysregulation and smoking abstinence. Two-level models will be conducted with 80 participants who complete the assessments over the 4 weeks of post-quit. The total number of EMAs are estimated to be 1792 ~ 2240 (80% to 100% compliance) clustered within 80 participants. The models will use an AR [1] error covariance structure to account for correlations between consecutive sleep and abstinence observations.[50] When *the outcome variable is smoking abstinence*, either sleep duration, bedtime, sleep latency, or sleep efficiency will be the predictor variable. When *the outcome variable is a nighttime sleep measure* (e.g., duration, sleep maintenance efficiency, sleep onset, sleep offset), daily smoking abstinence will be the predictor variable (alternatively, other cessation outcomes (e.g., urge) will be also tested). Variances for sleep dysregulation and abstinence measures will be decomposed to within-person and between-person components. Within-person variables will be centered at the person mean, so that positive values indicate scores higher than the person’s cross-day average. Between-person variables will be centered at the sample mean so that positive values indicate higher scores than others in the sample. A stepwise procedure will be used for variable selection, and variables from the procedure (e.g., sex, ethnicity, age, other tobacco/e-cigarette use, mental diagnosis, NRT use, BMI) will be included as covariates in all models. In addition, sensitivity analysis will be conducted to evaluate the robustness of the results from the analyses. We attend to sex as a biological variable by: 1) recruiting both sexes, 2) stratifying randomization by sex, and 3) exploring any differences in outcomes by sex.

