## Discussion

Sleep dysregulation is an understudied phenomenon and underappreciated intervention target for promoting smoking cessation and preventing relapse among smokers who want to quit.[20] Although several studies have demonstrated associations between sleep dysregulation and smoking behavior and cessation outcomes, limitations include using retrospective [1] or cross-sectional [27,31–33] survey methods focusing on singular sleep dimensions (usual sleep duration or quality), [1] testing a simple comparison (e.g., smokers vs. non-smokers, pre/post-tests) or using laboratory-based data collection, [21,34–36] and exclude lower SES adults who smoke. Thus, these studies provide only an “artificial lab-based” snapshot of behavior and focus on a single pathway. Our proposed study addresses these gaps by conducting a prospective, observational study to examine the bi-directional and temporal relationships between multiple dimensions of daily sleep dysregulation with smoking behavior and cessation outcomes during the quit attempt (both pre- and post-quit). Using repeated daily sleep measurements (i.e., objective sensor data via Actiwatch and subjective measures via daily diaries) and smoking-related variables, our study will provide a more granular understanding of the complex relationships between these variables in the real world. Aligned with NIDA Notice of Special Interest (NOSI), “Sleep and Substance Use Disorders,” this study will determine the mechanisms of the directionality of sleep dysregulation and smoking maintenance, withdrawal, abstinence, and relapse processes and will illuminate potential treatment targets for prevention and intervention, as they occur in real-time within natural settings for lower SES smokers.

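### The between-person sleep term is most likely averaged over the same post-quit days as abstinence, so under Hypothesis 1 it is partly a result of abstinence; the 14 pre-quit nights that would avoid this have no stated role.

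*Protocol article*

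**What the plan says.** Data collection covers both sides of the quit date. Under Study design and overview, "participants will complete daily EMAs for 2 weeks in the pre-quit period and for 4 weeks in the post-quit period". Under Procedure, participants "will wear an Actiwatch to obtain objective sleep data continuously for the entire 6-week study period". Each participant should therefore contribute about 14 nights of actigraphy before any abstinence is asked for.

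The models use a shorter window. Under Analytic approach: "Two-level models will be conducted with 80 participants who complete the assessments over the 4 weeks of post-quit", and "The total number of EMAs are estimated to be 1792 ~ 2240 (80% to 100% compliance) clustered within 80 participants".

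The same section says "Variances for sleep dysregulation and abstinence measures will be decomposed to within-person and between-person components". The within-person part is the deviation from the person's own average across days. For the other part, "Between-person variables will be centered at the sample mean so that positive values indicate higher scores than others in the sample". The section does not say which days enter the person's average, and it gives the pre-quit nights no role. The Discussion nevertheless presents the study as covering both the pre-quit and the post-quit period.

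Hypothesis 1 is that sleep is worse on nights after abstinent days, with the effect weakening over time. Hypothesis 2 is that a lapse is more likely on days that follow poor sleep.

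**The concern.** A between-person predictor should not be produced by the outcome it predicts. If the person's sleep mean is taken over the 28 modelled days, it includes the nights that abstinence has already altered. If Hypothesis 1 holds, people with more abstinent days have worse mean sleep because they were abstinent. Using that mean to predict abstinence then shows poor sleepers as more abstinent even when sleep has no effect.

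At stake is the between-person coefficient. The study sets out to separate the two directions between sleep and smoking, and this coefficient would mix them. The bias runs against an association of the Hypothesis 2 kind, so it can hide or reverse a real one. A reader using the results to decide which smokers to offer a sleep intervention would look at this coefficient. Sleep measured before the quit date is free of this feedback and is already being collected.

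**Working it through.** **1. The modelled window.** From the Analytic approach: 80 participants, 4 weeks, 80–100% compliance.

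- 80 × 28 = 2240, and 2240 × 0.8 = 1792. Both ends of the stated range reproduce exactly.
- A 42-day model would give 80 × 42 = 3360. The difference, 80 × 14 = 1120 person-days, is the pre-quit period.

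The pre-quit days are therefore outside the models as outcome days.

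**2. Why the mean is contaminated.** Let *s* be a person's usual sleep, *p* the proportion of abstinent days and *b* the effect of abstinence on that night's sleep. With a constant effect:

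- post-quit mean = *s* + *b·p* + error
- pre-quit mean = *s* + error

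If *s* and *p* are unrelated, the covariance of the post-quit mean with *p* is *b*·Var(*p*), which is non-zero whenever *b* is non-zero. For the pre-quit mean it is zero.

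**3. Size.** Simulation of 80 people with 14 pre-quit and 28 post-quit days, 1000 runs per case, and no effect of sleep on abstinence. The abstinent proportion was regressed on mean sleep (fractional logit, robust standard errors, two-sided 5%). These inputs are assumptions, not in the protocol: sleep ICC 0.4, total sleep SD 1 before the abstinence effect, person-level SD of the abstinence logit 2, and *b* either constant or fading as exp(−0.1 × day). At that fading rate, the average effect over 28 days is (1 − e^−2.8) / [28 × (1 − e^−0.1)] = 0.35 of its starting value.

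False significance of the between-person sleep term:

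| Effect of abstinence on sleep | Post-quit mean | 42-day mean | Pre-quit mean |
|---|---|---|---|
| −0.2 SD, constant | 16% | 11% | 6% |
| −0.3 SD, constant | 29% | 15% | 4% |
| −0.5 SD, constant | 61% | 33% | 6% |
| −0.2 SD, fading | 7% | 6% | 6% |
| −0.3 SD, fading | 10% | 8% | 5% |
| −0.5 SD, fading | 14% | 9% | 5% |

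Faster fading moves the post-quit figures towards the nominal 5%. The mean spurious log odds ratio for the post-quit mean is −0.20, −0.29 and −0.49 per unit of sleep (constant) and −0.07, −0.11 and −0.18 (fading). For the pre-quit mean it is about 0.

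**4. When a true positive association exists.** Abstinence logit raised by 0.8 per unit of usual sleep, constant *b*:

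| *b* | Log odds ratio, post-quit mean | Log odds ratio, pre-quit mean |
|---|---|---|
| 0 | 0.47 | 0.45 |
| −0.3 | 0.15 | 0.44 |
| −0.5 | −0.05 | 0.46 |

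**5. The within-person lagged term.** In the null scenarios above its mean estimate is at most 0.004, with rejection between 4% and 7%. The test of Hypothesis 2 as worded is essentially unaffected.

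**6. Pre-quit sleep as a covariate in the sleep models.** Under the same assumptions, regressing post-quit mean sleep on the abstinent proportion gives a standard error of about 0.23 for the between-person abstinence effect. Adding the pre-quit sleep mean lowers it to about 0.09, and the estimate stays centred on *b* (for *b* = −0.4 constant, −0.39 without the covariate and −0.40 with it).

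**The case against.** **Hypothesis 2 is not at risk.** It is a day-level statement, and no hypothesis is attached to the between-person part. This stands. A reader might infer that the main test of Hypothesis 2 is open to reverse causation. The documents do not support that, because the person-centred lagged term tests it and step 5 shows it is barely touched.

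**The window is inferred.** The article does not name the days, the figure of the models is not shown, and a fuller plan may settle it. This stands as a limit. The article does, however, fix the modelled window and the decomposition, and a 42-day mean would still be contaminated, though less.

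**A constant effect overstates the bias.** Hypothesis 1 itself expects weakening over time. This stands, so the upper figures are a worst case rather than the expected one.

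**Omitting the pre-quit days is sound.** A reader might infer that a third of the person-days is wasted. The stated aim is the first four weeks of the quit attempt, and participants are expected to smoke before the quit date. Leaving those days out as outcome days is therefore not an error. The gap is only that they are not used as a baseline.

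**The remedy changes the question and leaves confounding.** Sleep while still smoking is not the same quantity as sleep during the attempt, and shared causes such as dependence or mental health remain. This also stands. The pre-quit mean removes the feedback from post-quit abstinence and nothing more.

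**Conclusion.** The point holds for the secondary between-person coefficient only. If the person's sleep mean comes from the modelled post-quit days, which is the most likely reading, the coefficient linking mean sleep to abstinence is biased against an association of the Hypothesis 2 kind whenever Hypothesis 1 is true. For an assumed effect of 0.2–0.5 SD, false significance is about 15–60% if the effect is constant and about 5–14% if it fades, depending on how fast, against about 5% for the pre-quit mean. The error would mask or reverse a real association rather than create support for Hypothesis 2. All sizes rest on the assumed variances, effect and rate of fading, since the protocol gives no figures for them. Separately, ignoring pre-quit sleep in the sleep models gives up precision: a standard error of about 0.23 instead of 0.09, under an assumed sleep ICC of 0.4.

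**What to change.** 1. State which days form the person mean for each sleep measure.
2. In the abstinence models, use each participant's pre-quit mean of the same sleep measure as the between-person sleep term. Report the post-quit mean version as descriptive only.
3. In the sleep models, add the pre-quit mean of the same measure as a baseline covariate.
4. Keep the within-person terms and the 28-day outcome window as they are.
5. State that the between-person coefficient refers to sleep before quitting and is not causal, because shared causes remain.

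The cost is one derived variable per sleep measure and a few sentences of text, with no new data. The downsides are the change in what the coefficient describes and a slightly noisier mean from 14 rather than 28 nights. With no effect of abstinence on sleep, power for the true association in step 4 was 49.5% with the pre-quit mean and 51.4% with the post-quit mean.

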### Study hypotheses

Hypothesis 1. On days when participants are abstinent, they will be more likely to have poorer sleep health (shorter duration, later bedtime, longer latency, lower efficiency) that night due to withdrawal symptoms; however, the effect will be attenuated over time.

Hypothesis 2. On days when participants have slept more poorly (shorter duration, later bedtime, longer latency, lower efficiency), they will be more likely to lapse or relapse to smoking.

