**Table 1 pone.0334129.t001:** EMA Items of the study.

EMA	MEASURE
Morning Daily Diary	Cigarettes smoked
	Social interactions and support
	NRT use
	Side Effect Items
	Alcohol Consumption
	Sleep Items
End of Day Daily Diary	Cigarettes smoked
	Other substance use
	iCO Breath test
Random/Event EMAs	Recency of smoking
	Urge to smoke
	Stress
	Availability of cigarettes
	Recent alcohol use
	Cessation motivation
	Interaction with smokers
	Social setting/location
	Reasons for lapse
	Cigarette reward value
	Lapse warning signs

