A potential limitation of this study is that asking participants to complete EMAs may serve as an intervention (e.g., self-monitoring alone may improve health outcomes [51]. However, multiple EMA studies that have examined substance use disorders have found that EMA methods result in little to no reactivity.[52–54] A recent study of reactivity in smokers seeking cessation treatment found that frequent EMAs were related to lower craving, anxiety, anger, hunger, and positive affect but were unrelated to abstinence.[55] Importantly, all participants will receive equal numbers of EMAs in this observational study, and those variables will be centered at the person mean. Another limitation may be the burden of the 6-week EMAs and wearing of an Actiwatch. To mitigate this burden, we will use a watch with a long-lasting battery that does not require recharging during the 6-week study period. Additionally, sleep may be affected by the current season and data collection will span all four seasons (i.e., spring, summer, fall, and winter).[56,57] This study will include time of year as a covariate to avoid the potentially confounding effect of season. We indicated alternative strategies for secondary analysis using alternative outcomes (e.g., urge, cravings) for the study.

The proposed project will be among the first to examine associations between sleep dysregulation and smoking behavior and cessation outcomes using intensive longitudinal data via EMA and wearable sensors during a scheduled smoking cessation attempt. Improving sleep health in people attempting to quit smoking has emerged as a potential non-pharmacological candidate to improve cessation outcomes.[20] This project will provide preliminary data for a future R01 study focused on providing just-in-time adaptive sleep interventions (e.g., tailored messages) among lower SES adults who are attempting to quit smoking. For instance, Cognitive Behavior Therapy-based (CBT) just-in-time adaptive interventions (JITAI) that integrate sleep hygiene components [58] (e.g., maintaining a regular sleep routine, mindfulness training prior to the quit attempt, and/or CBT for sleep deprivation during cessation may be used to improve sleep health, which in turn may improve cessation outcomes. In addition, future studies may integrate other health behaviors that may mediate and/or moderate sleep dysregulation, smoking behavior, and cessation outcomes (e.g., physical activity or other substance use).

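### Covariates for the day-level hypotheses are left to stepwise selection with mostly person-level examples, where a prespecified set including day-level covariates is needed

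*Protocol article*

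**What the plan says.** Analytic approach: "A stepwise procedure will be used for variable selection, and variables from the procedure" form the adjustment set. The section then gives seven examples and the scope of their use: "e.g., sex, ethnicity, age, other tobacco/e-cigarette use, mental diagnosis, NRT use, BMI) will be included as covariates in all models". No entry or removal criterion is given, and this section forces no covariate in. It promises a sensitivity analysis without saying of what kind.

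The same section fixes the scale of the effects: "Variances for sleep dysregulation and abstinence measures will be decomposed to within-person and between-person components", and "Within-person variables will be centered at the person mean, so that positive values indicate scores higher than the person’s cross-day average". The hypotheses are day-level; H1 begins "On days when participants are abstinent, they will be more likely to have poorer sleep health".

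Two covariates are promised elsewhere. Procedure: "The use of personal vs. study-provided phones will be examined as a covariate in all analyses". Discussion: "This study will include time of year as a covariate to avoid the potentially confounding effect of season".

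Table 1 in Measures lists "Alcohol Consumption" and NRT use in the morning diary, and recent alcohol use in the random and event prompts. Alcohol and day of week are not named as covariates anywhere in the article.

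**The concern.** Stepwise selection lets the outcome data choose the adjustment set. It ranks a candidate by its association with the outcome, not by whether it is a confounder, a mediator or neither. Here that matters in two ways.

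First, the examples do not suit the main effects of interest. A person's sex, age, ethnicity, BMI or diagnosis is the same on abstinent and smoking days, so it cannot explain a difference between those days within that person. What can explain it is something that changes from day to day and acts on both smoking and sleep. Alcohol and day of week are the obvious cases.

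Second, a day-level variable can play different roles in the two directions. In H1 (abstinence, then sleep that night), drinking earlier in the day may lead to both smoking and poor sleep, which is confounding. In H2 (poor sleep, then lapse), drinking may lie on the path from the bad night to the lapse, which is mediation. One outcome-driven set for all models cannot tell these apart.

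At stake is bias in the within-person estimates that the study exists to produce and that are meant to inform a later intervention.

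**Working it through.** **Classifying the named covariates**

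| Covariate | Varies by day within a person? |
|---|---|
| Sex, ethnicity, age, mental diagnosis, BMI | No (5 of 7) |
| Other tobacco/e-cigarette use | Collected at the baseline visit (1 of 7) |
| NRT use | Yes, an EMA item (1 of 7) |
| Phone type (Procedure) | No |
| Time of year (Discussion) | Hardly, over six weeks |

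**Why person-level covariates do not help here.** A person-mean-centred predictor sums to zero within each person. It is therefore orthogonal to anything constant within that person. In a linear random-intercept model the within-person coefficient is then unchanged by adding such a covariate. In a logistic model or with AR(1) errors this is approximate.

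**Size of the shift if alcohol is left out of H1.** The article has no figure for this, so the inputs are assumptions:
- drinking on 10–30% of days;
- odds ratio for smoking on drinking days 2–3;
- smoking on 20% of non-drinking days;
- sleep worse by d = 0.3–0.5 day-to-day SD after drinking.

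The number of person-days is the article's lower figure: 80 × 28 × 0.8 = 1,792, which reproduces.

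Shift = d × [P(alcohol | smoking day) − P(alcohol | abstinent day)].

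Worked case (20% drinking, odds ratio 3, d = 0.5):
- Odds of smoking without alcohol 0.2/0.8 = 0.25; with alcohol 0.75, so P(smoke | alcohol) = 0.75/1.75 = 0.4286.
- P(smoke) = 0.8 × 0.2 + 0.2 × 0.4286 = 0.2457.
- P(alcohol | smoke) = 0.0857/0.2457 = 0.349; P(alcohol | abstinent) = 0.1143/0.7543 = 0.152. Difference 0.197.
- Shift = 0.5 × 0.197 = 0.099 SD.
- SE ≈ 1/√(1792 × 0.2457 × 0.7543) = 0.055, so the shift is 1.8 SE.

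| Drinking days | Odds ratio | d | Difference | Shift (SD) | Shift / SE |
|---|---|---|---|---|---|
| 10% | 2 | 0.3 | 0.071 | 0.021 | 0.37 |
| 20% | 3 | 0.5 | 0.197 | 0.099 | 1.8 |
| 30% | 3 | 0.5 | 0.244 | 0.122 | 2.3 |

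This SE treats all variation in abstinence as within-person. With the article's ICC range of 0.2–0.4 the ratios shrink by √0.8 to √0.6; the worked case becomes 1.6 to 1.4 SE.

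Direction: drinking days are more often smoking days and have worse sleep, so abstinent days look better slept. H1 predicts that they are worse slept, so the shift runs against it.

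**Simulation** (80 people, 28 days, linear random-intercept model, true within-person effect zero, 400 runs per setting; lapse log odds ratio for alcohol 0.8–1.5, sleep effect −0.1 to −0.3 SD):
- With no covariate, or with a person-level trait only, bias was identical to four decimals, between −0.014 and −0.085 SD for lapse days. Type I error was 0.04 to 0.44. The 0.44 arises at log odds ratio 1.5 (about 4.5), beyond the range used above. At log odds ratio 1.1 (about 3) and −0.3 SD, bias was −0.058 SD and type I error 0.21.
- With daily alcohol always in the model, bias was at most 0.005 SD in size and type I error 0.04–0.06.
- With alcohol kept only if p < 0.05, it was dropped in 47–48% of runs at −0.1 SD, 17% at −0.15 SD and none at −0.3 SD. Average bias under this rule stayed within 0.006 SD and type I error within 0.06.

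So the larger harm comes from alcohol not being a candidate at all. Chance dropping is frequent only where the bias is small. H2 was not quantified.

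**The case against.** The strongest reply is that the list is introduced as examples. Alcohol and weekday may be candidates in the full protocol, and a strong confounder that is offered will usually be retained. That stands: the article does not establish that alcohol is left out. It does establish the rule, and under that rule nothing day-level is guaranteed a place.

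Person-level covariates are also not useless. The models carry between-person terms, which age, sex or diagnosis can confound, and abstinence as an outcome is binary, so the orthogonality is only approximate there.

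Four stronger readings are tempting, and the article does not support them:
- *Stepwise selection makes the p-values for H1 and H2 too optimistic.* For person-level candidates it does not. Picking up noise traits leaves the centred estimate essentially unchanged in the linear model, and type I error was 5.0% with and without selection in a simulation of that case. Optimism could arise only through day-level candidates.
- *Each sleep measure or direction will get its own covariate set.* The text puts the selected variables in all models, which reads as one common set.
- *Phone type and season contradict the stepwise rule.* Both can be forced in beside selected covariates. The article should simply say so.
- *More than six predictors undermines the sample size.* Nine would need 205 independent observations by the article's method. Its own formula gives 80 × 28/(1 + 27 × 0.2) = 350 at its ICC of 0.2.

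Finally, putting same-day alcohol and NRT into every model could do harm. Poor sleep may lead to drinking and then lapse (H2); abstaining may change NRT use and then sleep (H1). That objection is sound and shapes the fix.

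**Conclusion.** The point holds as a matter of method. Outcome-driven stepwise selection, illustrated mainly by person-level traits, is a poor rule for day-level hypotheses with person-mean-centred predictors. A prespecified set that includes day-level covariates is better and costs only wording.

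If alcohol is not adjusted for, the H1 coefficient shifts by about 0.02–0.12 SD against the hypothesis, roughly 0.4 to 2.3 standard errors at 1,792 person-days and somewhat fewer once between-person variation in abstinence is allowed for. This rests wholly on assumed drinking frequency, odds ratio, sleep effect and 20% smoking rate on non-drinking days. If alcohol is offered and tested for retention, the expected bias is much smaller.

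A reader might infer that the planned tests are invalid or that alcohol has been excluded. The article shows neither. This should be changed before data collection, but it does not undermine the design.

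**What to change.** Replace the stepwise sentence with a covariate set fixed in advance, chosen by causal reasoning separately for each direction:

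- **All models:** weekend versus weekday and day since quit.
- **Daily alcohol and NRT use:** values timed before the exposure, for example prior-day values. Use same-day values only where they precede the exposure and are not mediators. State the choice for H1 and H2 separately.
- **Person-level, for the between-person terms:** age, sex, baseline cigarettes per day, phone type and season. Say in Analytic approach that phone type and season are forced in, so that it agrees with Procedure and Discussion.
- **Reporting:** show each within-person result with and without the daily alcohol and NRT terms. This could be part of the sensitivity analysis already promised.

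Cost: analysis-plan wording and a few extra fixed terms on about 1,800 person-days. Alcohol and NRT use are already EMA items, and weekday follows from the assessment date. Recruitment is planned from June 2026, and no new data item is needed for the daily terms.
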